**Fig. 1 Fig1:**
[figure not shown]
Trial data procedures and data workflow diagram. *euTP* external unblinded trial pharmacist, *ICF* informed consent form, *CRF* case report form, *DM* data management

### Outcome measures

#### Primary outcome measure

Our primary outcome is the proportion of adherent patients in the intervention group after three months of receiving SMS reminders of medication intake. For these purposes, we will assess patients’ adherence via combined adherence endpoint consisting of self-reported medication adherence measured via MMAS-8 and pill count rate (%).

The eight-item MMAS questionnaire, on which the MMAS-8 is based, evaluated hypertensive patients. It showed good reliability (α = 0.83) as well as sensitivity (93%) and specificity (53%) in the identification of lower versus higher adherence to antihypertensive medication. Additionally, the association between MMAS-8 and blood pressure control was proved statistically significant (*p* < 0.05) [19]. Each question aims at assessing a specific medication-taking behavior, either intentional or unintentional. The first seven questions have dichotomous answers (yes/no), whereas the last question offers a five-point Likert response. The range of the scores is from 0 to 8 with 0 being low adherence and 8 indicating full medication adherence [19, 74].

Pill count is a simple objective indirect measurement of patients’ adherence to medication intake [75]. AR will be calculated using the following equation:$$ \mathrm{A}\mathrm{R}\left(\%\right)=\left(\frac{\mathrm{No}.\mathrm{of}\;\mathrm{pills}\;\mathrm{actually}\;\mathrm{taken}}{\mathrm{No}.\mathrm{of}\;\mathrm{pills}\;\mathrm{that}\;\mathrm{should}\;\mathrm{have}\;\mathrm{been}\;\mathrm{taken}}\right)\times 100 $$

No specific guidelines exist on how to assess medication adherence [76]; therefore, we based our categorization of a patient as being “adherent” or “non-adherent” on the previous literature and expert opinions. Our study team agreed that a patient at the end of the trial will be considered as either “adherent,” having MMAS-8 ≥ 6 [19] and pill count rate ≥ 80% [77], or “non-adherent” if one or both of the previous conditions are not met. Table 3 contains details on our primary outcome measure.

**Table 3 Tab3:** Primary outcome Combined adherence endpoint

Level	
Domain	Combined medication adherence
Specific measurement variable	Adherence status (dichotomous) adherent: MMAS-8 score ≥6 and pill count rate ≥80% non-adherent: MMAS-8 score <6 and/or pill count rate <80%
Analysis Metric	Final value (Visit 2)
Method of aggregation	Proportion of adherent patients (%)
Time point of measurement	At Visit 2 (follow-up visit after 3 months of intervention period)

#### Secondary outcome measures

Table 4 summarizes the details of our secondary outcome measures. We will also evaluate the clinical outcome – blood pressure, which is highly emphasized to provide information on the relationship between medication adherence and blood pressure control [33]. Considering our trial population, consisting of older patients, we have decided to evaluate only systolic blood pressure, not diastolic blood pressure, in our secondary clinical outcome. First, diastolic blood pressure is known to paradoxically decrease with increasing age in patients aged above 55 years [78]. Second, diastolic blood pressure has shown to be less predictive in regard to decrease in cardiovascular morbidity and mortality [79]. We prepared a detailed guidance for blood pressure measurement (SPPA Scheme for Blood Pressure Measurement is available within Additional file 3) based on the current international recommendations for blood pressure measurement [4, 80]. Trial pharmacists will be re-trained on all steps and will comply with the SPPA Scheme for Blood Pressure Measurement during the whole trial, which will ensure that all blood pressure measurements will be performed uniformly.

**Table 4 Tab4:** Secondary outcomes

Secondary outcome	Change in medians of MMAS-8	Mean adherence rate after 3 months	Mean change in systolic blood pressure
Domain	Self-reported medication adherence (MMAS-8 questionnaire)	Medication adherence (pill count)	Blood pressure (manometer)
Specific measurement variable	MMAS-8 (categorical, ordinal)	Adherence rate in % (numerical, continuous)	Systolic blood pressure in mmHg (numerical, continuous)
Analysis Metric	Change from baseline (Visit 1)	Final value (Visit 2)	Change from baseline (Visit 1)
Method of aggregation	Median	Mean	Mean
Time point of measurement	Visit 1 Visit 2	Visit 2	Visit 1 Visit 2

We will also collect information on patients’ satisfaction with the intervention using our brief satisfaction questionnaire. The satisfaction questionnaire is based on previous studies [43, 71, 81, 82], stressing out the most important aspects for tailoring future mHealth trials to best reflect patients’ needs. Four pharmacists and a social psychologist assessed face validity of the questionnaire. Consequently, five patients aged above 55 years assessed the questionnaire for clarity, simplicity, and understanding. We adjusted the questionnaire according to their recommendations and comments. The final Satisfaction Questionnaire is included within Additional file 3.

#### Other outcome measures

We will collect the direct treatment costs associated with antihypertensive medication for each participant according to the current list of categorized drugs issued by the Ministry of Health of the Slovak Republic [83] on a monthly basis. We will actively collect reported signals of adverse events associated with antihypertensive medication during the whole trial duration.

### Participant timeline

Figure 2 summarizes all trial procedures.

**Fig. 2 Fig2:**
[figure not shown]
SPIRIT figure. *TP* trial pharmacist, *euTP* external unblinded trial pharmacist, *CG* control group, *IG* intervention group, *t*
_*0*_ time of enrolment in the trial, *t*
_*W*_ time of welcome SMS (one day after enrolment), *t* intervention duration (trial period), *t*
_*L*_ time of the last SMS reminder, *t*
_*1*_ time of the follow-up visit at the trial pharmacy

To minimize attrition of participants, trial pharmacists will contact all participants via phone call one day prior to their pre-scheduled follow-up visit as a reminder. During this phone call, the follow-up visit may be rescheduled to suit patient’s needs. If participants are not able to attend the follow-up visit at all, they will be asked to perform the pill count, MMAS-8, and the satisfaction questionnaire via phone call.

### Pilot test

Prior to trial initiation, a pilot test will be performed in one of the trial pharmacies with 20 patients, all receiving the intervention for two weeks. These patients will not be included in the final trial analysis. All procedures will be performed according to the SPPA trial protocol. The trial’s eligibility criteria and participation refusal rate will be assessed to ensure attainability of the planned sample size. SMS software will be tested, monitoring for any systematic errors, and a risk management protocol will be prepared. All data collection forms will be assessed with regard to comprehensiveness for trial participants and practical use for trial pharmacists, respectively. In cooperation with trial pharmacists and participants, we will evaluate the SMS wording for comprehensiveness, practicality, and patients’ perceptions. The data management team will test the data management pathway. Detected issues will be processed and the trial protocol will be revised, if necessary.

### Sample size calculation

In the recent multinational survey, adherence prevalence in European countries was in the range of 30–76% [25]. Given the results of the latest national study reporting even lower ARs [28], we assume 30% adherence prevalence in the control group. According to a meta-analysis of randomized clinical trials, SMS reminders had the potential to double the odds ratio (OR) of medication adherence (OR = 2.11; 95% confidence interval [CI] = 1.52–2.93; *p* < 0.001) in cardiovascular patients. The weighted mean effect size was d = 0.41 (95% CI = 0.23–0.59). After adjusting for publication bias, the odds of being adherent in the group receiving SMS reminders was 68% higher than in the control group (OR = 1.68; 95% CI = 1.18–2.39) [50]. Results of the StAR trial carried out in a hypertensive population support these results, reporting an OR of 1.86 (95% CI = 1.20–2.16; *p* = 0.002) for improved adherence in patients receiving SMS reminders [84]. Therefore, we hypothesize that SMS reminders of antihypertensive medication intake can improve the proportion of adherent older patients in Slovakia from 30% to 49% given an effect size of w = 0.2 (equivalent to d = 0.4). Using a χ2 test of independence, a total of 264 patients are needed to reject the null hypothesis that the adherence proportions in both groups are equal with a power of 0.9 and alpha of 0.05. Considering approximately a 10% attrition rate, we plan to enroll 300 patients (150 in each group). Previous studies reported attrition rates of 3.2% [71], 12.8% [84], and 19.0% [70]; while the major reason for loss of participants was unwillingness or impossibility to attend the follow-up visit(s). Slovak chronic hypertensive patients are already used to regular visits of pharmacies in approximately three-month cycles. Since our trial is embedded within usual pharmaceutical care provision, we expect a lower drop-out, as in the EmPhAsIS study [85].

The planned sample size is sufficient to detect a difference in adherence of 1 point on the MMAS-8 scale, which is our secondary outcome. Provided that the median MMAS-8 score in the control group is 4 and in the intervention group 5 (SD = 1.8) [30], using a two-tailed t-test, we need 172 participants to achieve a power of 95% and significance level of 5%. For our secondary clinical outcome (mean change in systolic blood pressure), this sample size lacks sufficient power to detect a clinically meaningful change of at least 5 mmHg (SD = 20) with a power = 0.9, alpha = 0.05 (using either mixed analysis of variance or analysis of covariance test). A larger sample is currently not feasible; however, the SPPA trial focuses primarily on adherence to medication. If the results of this trial show sufficient effectiveness of SMS reminders in increasing prevalence of adherent older hypertensive patients and patients’ satisfaction is high, we will conduct a larger study focusing on clinical outcomes. Sample size calculations were carried out using G*Power software version 3.1.9.2.

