## Methods

### Trial objectives

The primary objective of the SPPA trial is to assess if daily SMS reminders of antihypertensive medication intake provided by pharmacists in addition to the sPhC increase the proportion of adherent older hypertensive ambulatory patients.

Secondary objectives include: (1) comparing the change of self-reported adherence using the eight-item Morisky Medication Adherence Scale (MMAS-8); (2) comparing ARs measured via pill count between trial groups; (3) comparing the change in systolic blood pressure; (4) investigating the effect of SMS reminders on improving patients’ adherence and systolic blood pressure control (treatment effects) across subgroups; and (5) collecting and reporting patients’ satisfaction with daily SMS reminders.

We will report up-to-date ARs of older hypertensive patients in Slovakia and assess the impact of sociodemographic characteristics on patients’ adherence to antihypertensive medicines. Furthermore, we will evaluate the MMAS-8 questionnaire in our trial population. Additionally, we will carry out a simple cost-effectiveness analysis from the payers’ perspective.

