### Exclusion criteria

Exclusion criteria assessed prior to patient enrolment:Planned hospitalization during the trial period;Biological impairment affecting the ability to read the SMS (e.g. loss of vision, visual field cuts, aphasia);Living in the same household with another trial participant;Participation in another clinical trial.

Exclusion criteria assessed after patient enrolment:Hospitalization during the trial period;Patient informs he/she will not be able to participate in the trial;Withdrawal of informed consent.

We have strived to maintain broad eligibility criteria to ensure our trial population best reflects the real-world population of patients for whom the intervention is intended. Nevertheless, we accepted some inclusion and exclusion criteria, which can strengthen the validity of the trial’s results while not introducing selection bias. We focus on patients with primary hypertension to limit the confounding influence of secondary hypertension causes both on patients’ adherence to medication and resulting blood pressure control. Patients with other co-morbidities are eligible to participate in the study. We will recruit patients while filing their prescription at the trial pharmacy. According to Slovak health legislation, physicians are allowed to prescribe medication to chronic patients for a maximum of three months. Hence, patients who are collecting their medicines at the day of the recruitment will in most cases begin to take the pills out of the collected medication package on the next day (first day of the intervention), enabling the precise calculation of pill count rates. Furthermore, chronic patients in Slovakia visit the pharmacy usually in three-month cycles. We will include only patients who take their antihypertensive medication for at least one year because these patients are considered to have reached their acceptance phase of medicinal treatment and consequently are at lower risk of early therapy discontinuation due to non-acceptance [66]. Trial participants hospitalized during the trial will be excluded since during their hospital stay healthcare providers will manage their medication resulting in the redundancy of SMS reminders.

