### Data collection, handling, and monitoring

Trial data will be collected at Visit 1 (day of patient enrolment) and at Visit 2 (follow-up visit after three months). Table 2 provides and overview of all case report forms that will be used in the trial for data collection. Furthermore, we will actively seek and collect signals of adverse events associated with antihypertensive medication intake reported by the participants. We will also collect anonymous reasons for participation refusal and discontinuation of participation. All trial forms and materials constituting the Appendixes of the SPPA trial protocol are available in Additional file 3.

**Table 2 Tab2:** Overview of Case Report Forms in the SPPA trial

Case Report Form/Questionnaire	Details	Time Point
Case Report Form Visit 1 – PART A	Antihypertensive medication specification Mobile phone number for SMS reminders Preferred time of SMS reminder	Visit 1
Case Report Form Visit 1 – PART B	Blood pressure measurement	Visit 1
Case Report Form Visit 1 – PART C	Medication adherence measurement via MMAS-8	Visit 1
Case Report Form Visit 1 – PART D	Patient information (Sociodemographic and health information, information on mobile phone usage)	Visit 1
Case Report Form Visit 2 – PART A	Medication adherence measurement via pill count	Visit 2
Case Report Form Visit 2 – PART B	Blood pressure measurement	Visit 2
Case Report Form Visit 2 – PART C	Medication adherence measurement via MMAS-8	Visit 2

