#### Other outcomes analyses

We will assess internal consistency of the MMAS-8 scale in our trial population by Cronbach’s alpha coefficient and reliability of the summed score by McDonald’s hierarchical omega, which has been shown to be a superior measure to Cronbach’s alpha [97]. We will also provide the measures of sensitivity and specificity of MMAS-8 related to correct prediction of high blood pressure. Of interest is also the relationship between two measures of adherence (MMAS-8 and pill count), which will be analyzed using correlation coefficients (Pearson and Kendall tau). Additionally, regression techniques to analyze the impact of co-variables, such as: age, gender, education level, social status, place of residence, number of daily doses, co-medication, co-morbidities (concomitant diseases, smoking status), and pharmacy on patients’ adherence will be applied.

Since we are interested in providing relevant information for the decision-making process, we will conduct a simple cost-effectiveness analysis. Here, we will focus only on the differential costs that depend on the choice of alternative care (usual pharmaceutical care or SMS reminder).

Finally, we will collect, report, and perform a qualitative analysis of the refusal to participation in the trial and withdrawal from the trial rates.

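### Satisfaction with the reminders is described as collected only from patients still in the trial at three months, so it can be overstated if some leave because of the daily messages

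*Protocol article*

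**What the plan says.** Satisfaction has two roles in the protocol article. Under Trial objectives, the fifth secondary objective is to collect and report patients' "satisfaction with daily SMS reminders". Under Sample size calculation it becomes a condition for further research: if the reminders prove effective on adherence and patient "satisfaction is high, we will conduct a larger study focusing on clinical outcomes".

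On timing, the section on data collection, handling and monitoring fixes two collection points, enrolment and the three-month follow-up visit. The Participant timeline section adds a substitute for participants who cannot attend that visit: "they will be asked to perform the pill count, MMAS-8, and the satisfaction questionnaire via phone call". The text describes no questionnaire at discontinuation.

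On patients who leave, the exclusions assessed after enrolment include "Patient informs he/she will not be able to participate in the trial" and "Withdrawal of informed consent", alongside hospitalisation. Their reasons are handled separately. The data collection section says "We will also collect anonymous reasons for participation refusal and discontinuation of participation", and Other outcomes analyses plans to "perform a qualitative analysis of the refusal to participation in the trial and withdrawal from the trial rates". Neither statement connects those reasons with the satisfaction result.

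**The concern.** For a daily message, leaving the trial because of the messages is a strong sign of dissatisfaction. Under the plan as described, a patient who does this before three months is never asked, is listed as excluded, and gives a reason that is not tied to the satisfaction score. The result then describes those who tolerated the messages rather than all who were assigned to them.

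At stake is a planning decision, namely whether to run a larger study with this intervention, and how acceptable the reminders are said to be in routine use. The section on patients' satisfaction also uses the score to predict change in adherence and blood pressure. That analysis would lose its least satisfied patients for the same reason. The comparison of adherent proportions between arms is a separate matter and is not touched.

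**Working it through.** The plan states no satisfaction figure, so there is none to reproduce. The check is a bound, preceded by a reading of the safeguards.

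**Inputs from the article (Sample size calculation).** 150 patients per arm; planned attrition about 10%; attrition in three earlier studies 3.2%, 12.8% and 19.0%. The plan's attrition allowance is consistent: 264 / (1 − 0.10) = 293.3, so 294 are needed and 300 are enrolled. At 10%, 150 × 0.10 = 15 patients are lost from the reminder arm.

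**Inputs assumed here.** The share of assessed patients who are satisfied, S_obs, is taken as 80%, with a range of 70% to 90%. Treating satisfaction as a proportion is a simplification, since the article plans a multi-item scale.

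**Formula.** With loss d and satisfaction S_lost among those lost, the figure for all assigned is

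S_all = (1 − d) × S_obs + d × S_lost,

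and the overstatement is d × (S_obs − S_lost).

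**At the planned 10% loss, S_obs = 80%:**
- Every leaver dissatisfied (S_lost = 0): 0.90 × 0.80 = 0.72, an overstatement of 8 points.
- Half dissatisfied, the rest like completers (S_lost = 0.40): 0.72 + 0.10 × 0.40 = 0.76, an overstatement of 4 points.
- Leavers like completers (S_lost = 0.80): 0.80, no overstatement.

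**Over the attrition rates named in the article:**

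| Loss | S_obs = 80%, all leavers dissatisfied | S_obs = 80%, half dissatisfied | Largest overstatement for S_obs 70% to 90% |
|---|---|---|---|
| 3.2% | 77.4% | 78.7% | 2.2 to 2.9 points |
| 10% | 72.0% | 76.0% | 7.0 to 9.0 points |
| 12.8% | 69.8% | 74.9% | 9.0 to 11.5 points |
| 19.0% | 64.8% | 72.4% | 13.3 to 17.1 points |

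The columns with every leaver dissatisfied are outer limits. They count as dissatisfied even patients lost through hospitalisation, who have no reason to be.

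**Would the existing provisions repair it?**
- *Imputation (Statistical analysis).* Chained equations are stated in general terms, with blood pressure and MMAS-8 as examples. Satisfaction with the reminders has no baseline value, so imputed values would come from completers with similar characteristics. That is adequate only if, given those characteristics, leaving is unrelated to satisfaction, which is the very point in doubt.
- *Intention to treat.* The principle is stated for all analyses, but it cannot supply a satisfaction value that was never collected.
- *Phone substitute.* It reaches patients who cannot attend at three months. It is not described for patients who have already left.
- *Reported reasons.* They show why patients left, but reasons not linked to a trial code and arm cannot enter a figure for all assigned patients.

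**The case against.** The strongest reply is that nothing in the article shows that the messages drive patients out. The Sample size calculation section gives reluctance or inability to come to follow-up visits as the main reason for loss in earlier studies, and the phone substitute is aimed at much of that loss. This stands. A reader might infer that the satisfaction figure **is** biased upwards. The documents do not support that, because direction and size depend on reasons for leaving that are not yet known.

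Second, withdrawals are not hidden. Missing data are to be reported with reasons and patterns, withdrawals analysed qualitatively, and reasons for withdrawal published. This also stands, and it means a careful reader of the results would see message-related withdrawals beside the score. It does not provide a rule for combining the two.

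Third, a reader might infer that the next study hinges on this one number. The article does not go that far. It gives no threshold for high satisfaction, and the Discussion words the conditions for further research more broadly, naming clinical benefit, feasibility, acceptance by patients and cost-effectiveness. Whether an overstatement of a few points would change the decision cannot be judged.

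Fourth, Figure 2 and Additional file 3 are not shown and may give more detail on when the questionnaire is used. The point is therefore limited to what the article describes.

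Finally, the phone contact at follow-up is made by the trial pharmacists, who are the blinded assessors. Having them ask about reminders when a patient discontinues could reveal the allocation. This is correct, and it determines who should ask.

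**Conclusion.** The point holds in conditional form. As described, satisfaction is measured only in patients who reach the three-month contact, and those who discontinue have no route into the result. The figure can be too high if some leave because of the messages, and the stated imputation would not correct that.

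The size is unknown. At the planned 10% loss and an assumed 80% among completers, the overstatement lies between 0 and 8 points, with 4 points if half of the leavers are dissatisfied. The 80% and the split among leavers are assumptions made for illustration, not estimates. Since the outcome is descriptive and feeds a later planning decision, and the primary comparison is unaffected, importance is low to moderate.

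**What to change.** 1. Report satisfaction with all patients assigned to reminders as the denominator, next to the completers' figure. Show patients who were not assessed as a separate category, by reason.
2. Add a sensitivity analysis that counts only message-related discontinuations as not satisfied. Hospitalisation and other unrelated losses should not be counted this way.
3. Record the reason for discontinuation and the arm against the trial code, out of the trial pharmacists' sight. Reasons for declining to enter the trial can stay anonymous.
4. Offer the short satisfaction questionnaire at discontinuation unless the patient refuses contact. The project leader should do this, not the trial pharmacists. The Blinding section already makes the project leader the participants' contact, accepts that allocation may become known there, and keeps that role out of outcome assessment and the final analysis.

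The cost is a few extra calls (at the planned 10% loss, at most about 15 in the reminder arm), a line on the discontinuation record and a sentence or two of analysis text. The satisfaction figure may come out less favourable.
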